### Sample size

This study is a superiority testing trial (one-tailed trial) of which the primary outcome is the number of retrieved LNs and study subjects will be divided into 4 groups. Combined with our previous findings and literature reports, the standard deviation σ of the total number of LNs in control group was 8.6 [9, 13, 17]. The *α* (test level) is set as 0.05 and power (1-β) is 0.8. A difference of more than 3 in the total number of detected LNs will be considered as significant, i.e., the effect value *d* = 3/*σ* = 0.35. Thus, at least 103 (102.3) participants are required in each group. Considering an expected dropout rate of 20%, 129 (128.75) participants are finally required in each group, leading to a total of 516 participants.

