### Outcome

The primary outcome is the total number of retrieved LNs. The secondary outcomes include positive rate, false positive rate, negative rate, false negative rate, number of metastatic LNs, rate of LN metastasis, relationship between LN metastasis and dual staining, morbidity and mortality, 3-year disease-free survival rate, 3-year overall survival rate, 3-year recurrence rate, postoperative recovery, duration of surgery, changes in body weight, intraoperative blood loss, intraoperative mortality, incision length, body temperature, and changes in lab parameters (albumin, prealbumin, hemoglobin, white blood cells, C-reactive protein, etc.).

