### Data analysis

Database will be established using Epidata 3.0, and statistical analysis will be performed using SPSS 18.0. This trial uses differential testing; a *p*-value less than 0.05 will be considered statistically significant, and the confidence intervals for the parameters will be estimated as 95%.

In this trial, validity analysis based on MITT (modified intention to treat) analysis will be conducted. The primary and secondary outcomes will be analyzed with both MITT and PP (per protocol) analysis. Conclusion of MITT analysis will be the primary analytical method, and if the conclusions of PP analysis and MITT analysis are consistent, the credibility of the conclusions can be improved. SP (safety population) analysis will be used to analyze laboratory evaluations, adverse events, and adverse reaction data. SP will be defined as the denominator for the incidence of adverse reactions.

Descriptive statistics will be used to systematically describe primary and secondary outcomes. Means, standard deviations, and confidence intervals will be presented based on data from the control group and intervention groups. Frequency distributions, percentages, medians, and mean rank order will be presented based on quantitative data and rank data. Positive rates, positive number, and total number of retrieved LNs will be presented based on qualitative data. The number of events, number of missingness, median survival time, and survival rate will be presented based on survival data. Efficacy analysis will be performed on data following descriptive statistics. This study utilizes Pearson chi-square test for qualitative data, *t* test for quantitative data, Wilcoxon rank sum test for ranked data, Log-rank test for univariate analysis and Cox regression model for multivariate analysis of survival data, and two-tailed test for safety indicators and incidence of adverse reactions.

Abnormal values will be judged when the observed value is greater than P75 or less than P25, and 3 times more than the interquartile range defined as P75 subtracts P25. Sensitivity analysis will be performed on the abnormal data, and the data will be retained if results are not contradictory. If there is a contradiction, specific analysis will be conducted.

Subgroup analysis will be performed to identify risk factors for the prognosis according to the specific circumstances of the data.

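### The outlier rule settles the handling of extreme values after the results are known, and its cut-off is ambiguously worded; the exposure lies in skewed secondary outcomes

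*Protocol article*

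**What the plan says.** The rule is in the Data analysis section of the protocol article and has three parts.

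- **Definition.** There are two conditions. The first reads: "Abnormal values will be judged when the observed value is greater than P75 or less than P25". The second is a multiple of three of the IQR, but what is to be compared with that multiple is not stated.
- **When results agree.** A sensitivity analysis is run on the abnormal data, and "the data will be retained if results are not contradictory".
- **When results disagree.** "If there is a contradiction, specific analysis will be conducted". The content of that analysis is not given, nor which result then governs.

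The same section assigns the t test to quantitative data and the rank-sum test to ranked data. It makes MITT the primary analysis and PP supportive. The Outcome section names the total node count as primary and lists blood loss, duration of surgery and postoperative recovery among the secondary outcomes. Under Postoperative parameters, recovery includes drainage volumes and hospital stay. The Study design section describes the trial as unblinded.

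**The concern.** A sensitivity analysis should show how far a fixed main result depends on a few extreme values. Here its result helps decide what the main data are. Where the two analyses agree, the choice is harmless. Where they disagree, the plan leaves the choice open at a point when both p-values are on the table. Ranking MITT above PP does not close the gap: it ranks populations of patients and does not say whether flagged values stay in the MITT data.

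The unclear cut-off adds to this, because the two possible readings flag very different shares of the data. At stake are the error rate of comparisons on skewed outcomes and the credibility of any result that turns on a few patients.

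**Working it through.** **1. Evaluable number per arm.** The Sample size section gives SD 8.6, a difference of 3, one-sided α 0.05 and power 0.80. A one-sided two-sample t test with d = 3/8.6 = 0.349 needs 102.3, so 103 per arm. Then 103/0.8 = 128.75, so 129, and 4 × 129 = 516. The stated figures reproduce and are not affected by this point. I use 103 per arm below.

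**2. Primary outcome under the likely meaning** (below P25 − 3 × IQR or above P75 + 3 × IQR), taking node counts as roughly normal with SD 8.6:

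- IQR = 2 × 0.6745 × 8.6 = 11.6, and 3 × IQR = 34.8.
- Distance of the fence from the mean = 5.8 + 34.8 = 40.6, so z = 40.6/8.6 = 4.72.
- Two-sided probability = 2.3 × 10⁻⁶, or 0.001 expected values among 516.

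With negative binomial or lognormal counts of the same SD, at assumed means of 30 and 40, the share is at most about 0.12% (516 × 0.0012 ≈ 0.6 values). The full and trimmed data would almost always be identical.

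**3. Skewed secondary outcomes under the same fence.** The document gives no distributions for these. I assume lognormal data with median 1 and log-SD s. Then P25 = exp(−0.6745s), P75 = exp(0.6745s), and the upper fence is P75 + 3(P75 − P25). The lower fence is negative, so it flags nothing.

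| s | P25 | P75 | IQR | Upper fence | ln(fence)/s | Share above |
|---|---|---|---|---|---|---|
| 0.5 | 0.714 | 1.401 | 0.687 | 3.463 | 2.48 | 0.65% |
| 0.9 | 0.545 | 1.835 | 1.290 | 5.705 | 1.93 | 2.65% |

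With quartiles estimated from the sample, simulation gives 0.7% and 2.7%.

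**4. Effect of a free choice between the two analyses.** Simulation settings: two arms of 103, no true effect, two-sided t test at 5%, quartiles taken over both arms together, 8,000 data sets per setting. The full and trimmed analyses disagree on significance in about 3% (s = 0.5) to 7% (s = 0.9) of data sets. The chance that at least one is significant is

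(full-data error + trimmed-data error + disagreement rate)/2.

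- s = 0.5: (5.1 + 5.0 + 3.0)/2 ≈ 6.5%.
- s = 0.9: (4.8 + 5.0 + 6.7)/2 ≈ 8.2%.

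Across runs the range is about 6.5–8.5%. The Monte Carlo standard error near 8% is √(0.08 × 0.92/8000) ≈ 0.3 points. A repeat with 80,000 data sets per setting gave 6.5% and 8.0%.

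Either analysis fixed in advance holds close to 5%. All of the excess comes from choosing between them.

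**The case against.** **The text never says that flagged values are deleted.** That stands. It says they are kept if results agree; it does not state the converse. The 6.5–8.5% assumes that the significant analysis is chosen in every disagreement, which the plan does not prescribe, so it is a ceiling for this mechanism.

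**Detail on divergent sensitivity analyses is commonly left to the SAP.** This is true of the content of the further analysis. But the article does not merely stay silent: it makes retention depend on agreement. A later plan would have to replace that rule, not just fill it in.

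**A stronger reading is tempting and should not be adopted.** Taken literally, "observed value is greater than P75 or less than P25, and 3 times more than the interquartile range" could mean that the node count itself is compared with 34.8. A reader might infer that a quarter of node counts would be flagged, that the high counts the tracers are meant to produce would be removed, and that power would fall to about 48–57%. The documents do not support this:

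- The wording is more plausibly an imprecise statement of the usual extreme-value fence.
- The share depends on a mean node count, which the document does not give. It is 4% at an assumed mean of 20, 13% at 25, 25% from 29 to 40.6, 38% at 45 and 46% at 50, so a quarter is neither a stated figure nor an upper limit.
- The power figure also assumes means of 25–30 and automatic deletion of every flagged value.

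These numbers show only why the wording needs to be made exact.

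**Conclusion.** The point holds in a limited form. The plan states a result-dependent rule for extreme values, leaves the disagreement branch undefined and does not keep the all-values analysis primary. Its cut-off can be read in two ways.

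Under the likely reading the primary comparison is practically unaffected. For skewed secondary outcomes the worst-case rise in two-sided error is from 5% to about 6.5–8.5% per comparison. That rests on assumed lognormal data with log-SD 0.5 to 0.9, 103 per arm, pooled quartiles and an analyst who always takes the significant result. With less skew, or a choice not driven by significance, the rise is smaller. The rule should be corrected, but it does not threaten the trial's main conclusion.

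**What to change.** Replace the rule in the Data analysis section with wording to this effect:

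> All verified values are kept in the main MITT and PP analyses. Values below P25 − 3 × IQR or above P75 + 3 × IQR are checked against source and changed only for a documented error. An analysis without the flagged values is reported beside the main result as a sensitivity analysis, whatever it shows.

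Using the rank-sum test, already named in the plan, for clearly skewed secondary outcomes would reduce the influence of extreme values, but it is optional.

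The cost is a few sentences and one sensitivity table, with no effect on patients, procedures or sample size. The downside is that the main analysis keeps some noisy but genuine values. The Protocol amendments section provides the route, and the change should be made before outcomes are compared by arm.

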### Oversight and monitoring

#### Date monitoring

The members of the DMC (data monitoring committee) will be independent from the trial sponsor and trial personnel. A senior data statistician will serve as the chairman of the committee, and the rest will be composed of independent data statisticians and clinical scholars. The DMC will hold a Data Monitoring Reporting Meeting in February of each year during the conduct of the trial. In addition to members of DMC, clinical investigators, statisticians, and supporting assistants of the trial will participate in the meeting and provide reports. Data monitoring will be completed by comparing the original data to confirm the completion status of data collection.

#### Adverse event reporting

The evaluation of adverse events and serious adverse events is based on Common Terminology Criteria for Adverse Events v3.0. The study director must report adverse events or serious adverse events to the study committee and the healthcare department of the province (city) according to relevant laws and regulations. Serious adverse events should also be reported to the head of the medical institutions and corresponding reporting procedures shall be completed in accordance with relevant provisions. Adverse events with emergency reporting obligation are as follows: (1) all patients who died during treatment or within 30 days from the last treatment day (regardless of causal relationship with the study protocol treatment) and (2) patients with unexpected grade 4 non-hematological toxicities. Adverse events with regular reporting obligations are as follows: (1) death causally related to treatment 31 days after the last treatment day, including death suspected to be related to treatment (including death caused by obvious primary disease); (2) expected grade 4 non-hematological toxicities; (3) unexpected grade 3 adverse events; (4) other major medical events such as adverse events considered by the trial team to have an potentially, permanent, and significant impact on patients’ offspring. Adverse events in items (2) to (4) above will be reported periodically if any definite or possible causal relationship to the study is identified.

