#### Postoperative parameters

The following information will be recorded: (1) pathological findings including histological type, distant metastasis and location, NIH risk grade, and degree of radical surgery (R0/R1/R2); (2) postoperative complications of which the severity is graded according to the Clavien-Dindo system and serious complication is defined as grade III or above; (3) lab parameters including blood routine test (hemoglobin, red blood cells count, white blood cells count, lymphocyte count, neutrophil count and percentage, platelets count, monocyte count, etc.) and blood biochemistry (albumin, prealbumin, total bilirubin, indirect bilirubin, direct bilirubin, AST, ALT, creatinine, urea nitrogen, total cholesterol, triglyceride, fasting blood glucose, potassium, sodium, chloride and calcium, etc.); (4) postoperative recovery including time to first ambulation, time to first ventilation, time to liquid diet, postoperative highest body temperature, time to gastric tube withdrawal, daily gastric juice drainage volume, time to abdominal drainage tube withdrawal, daily abdominal drainage tube drainage volume, blood transfusion volume from the surgery to discharge, and postoperative hospital stay.

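### The late-death reporting item for treatment-related deaths also takes in deaths obviously due to the cancer, and the grade 4 items leave out haematological events that the grade 3 item covers

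*Protocol article*

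**What the plan says.** The section Adverse event reporting opens with the grading scale ("The evaluation of adverse events and serious adverse events is based on Common Terminology Criteria for Adverse Events v3.0") and a general duty: "The study director must report adverse events or serious adverse events to the study committee and the healthcare department of the province (city"). It then sets out two lists.

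- **Emergency list.** Item (1) is "all patients who died during treatment or within 30 days from the last treatment day (regardless of causal relationship with the study protocol treatment"). Item (2) is "patients with unexpected grade 4 non-hematological toxicities".
- **Regular list.** Item (1) is led by a causal condition, "death causally related to treatment 31 days after the last treatment day". The same item is then widened by a clause with its own bracket: "including death suspected to be related to treatment (including death caused by obvious primary disease"). Item (2) is the expected counterpart of the grade 4 emergency item and is again limited to non-haematological toxicity. Item (3) is "unexpected grade 3 adverse events", with no limit by organ class. Item (4) is an open category of other major medical events, whose one example concerns lasting effects on patients' offspring.

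A closing sentence makes items (2) to (4) reportable where a definite or possible causal link to the study is found. It does not mention item (1).

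**The concern.** Two things look wrong in the printed lists.

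First, the late-death item is defined by a causal or suspected causal link to treatment, yet its bracket brings in deaths whose obvious cause is the primary disease. A site that follows the text would put cancer deaths and suspected treatment deaths under one item. Late cancer deaths must be expected here. Eligibility runs to cT4a with any nodal status (Inclusion criteria), follow-up lasts to month 36 (Follow-up records), and 3-year survival and recurrence are secondary outcomes (Outcome). An item meant to show late harm from surgery or tracer would then carry deaths that say nothing about either.

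Second, the severity order is inverted for one class of event. An unexpected haematological event has a named category at grade 3 and loses it at grade 4. Haematological values are collected throughout (Postoperative parameters, and Table 1 under Follow-up records), so the class is not hypothetical.

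At stake is the clarity of the safety reporting. A committee receives adverse-event reports every 8 months and advises on whether enrolment continues (Interim analysis).

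**Working it through.** The plan states no figure on this point, so there is nothing to recompute. The check is a cross-classification of the two lists as written.

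**Deaths, by timing and cause**

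| Death | Where it falls |
|---|---|
| During treatment or within 30 days, any cause | Emergency (1) |
| Later, related or suspected to be related to treatment | Regular (1) |
| Later, obviously due to the primary disease | Regular (1), through the bracket |

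1. Emergency item (1) expressly disregards cause. Regular item (1) is worded by causal relation. The lists therefore distinguish all-cause from causal reporting, and the late item belongs to the causal kind.
2. The bracket in regular item (1) admits deaths that its own leading words shut out.
3. The closing causality condition names items (2) to (4) only, so it does not remove those deaths from item (1).
4. No other section of the article defines the item differently.

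**Non-fatal events, by grade, expectedness and class**

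| Event | Haematological | Non-haematological |
|---|---|---|
| Grade 4, unexpected | Not named | Emergency (2) |
| Grade 4, expected | Not named | Regular (2) |
| Grade 3, unexpected | Regular (3) | Regular (3) |
| Grade 3, expected | Not named | Not named |

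Four of the eight cells are named and four are not. The two expected grade 3 cells are no anomaly, since leaving expected lower-grade events off a list is an ordinary choice. The inversion lies in the haematological column: the unexpected event is named at grade 3 and not at grade 4. In the non-haematological column the order runs the right way, with regular reporting at grade 3 and emergency reporting at grade 4.

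Here, not named means without an explicit category. Regular item (4) is open-ended and could be read to take in a grade 4 haematological event, and the general duty applies to every cell.

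**The case against.** The strongest reply is that little is lost in practice. The general duty covers adverse and serious adverse events without limit by grade or class. Serious events also go to the head of the institution. Item (4) is open, and the 8-monthly report in Interim analysis includes adverse and serious adverse events. The section also defers to laws, regulations and guidelines that are not shown. This stands against any claim that a grade 4 haematological event has no reporting trigger, which a reader might infer from the two lists alone. It does not give such an event a category, and it does not touch the death bracket.

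A second reply is that the bracket can be read cautiously: a suspected treatment death still counts even where the primary disease is an obvious cause. That reading is possible, but the words do not say it, and a site could as readily file every late cancer death there.

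A reader might also infer that true late treatment deaths would be hidden. The documents do not support this. Over-inclusion adds noise but suppresses no report, and no section takes a treatment-related-death endpoint from this item. Safety is analysed in the safety population (Data analysis), and morbidity, mortality and survival are separate outcomes (Outcome).

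Finally, a reader might set the lists against the rule in Postoperative parameters that "serious complication is defined as grade III or above" and see a conflict over expected grade 3 events. That rule uses Clavien-Dindo and the lists use CTCAE v3.0. A grade on one scale need not match the same grade on the other, so no contradiction is shown.

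**Conclusion.** The point holds in limited form. The bracket in regular item (1) contradicts the item's leading words, and nothing else in the article resolves it. Read literally, it mixes late cancer deaths with treatment-related deaths and weakens that safety signal. The grade 4 wording is a gap with an inverted severity order rather than a strict contradiction, and its effect is confined to the missing explicit category for haematological events.

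The size cannot be stated as a percentage. The article gives neither a cancer mortality rate nor a rate of late treatment-related death, so any share of misfiled reports would rest wholly on assumed rates and on every late cancer death being filed under the item. The direction rests only on late cancer deaths occurring during follow-up and on sites applying the bracket as printed.

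Neither defect affects the primary outcome, sample size or primary analysis. Both should be corrected because these are operative safety rules and the correction is small.

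**What to change.** 1. In regular item (1), reconcile the bracket with the item's leading words so that deaths obviously due to the primary disease are excluded. Record those deaths, with an attribution of cause, under survival follow-up.
2. Reconcile the grade 3 and grade 4 items so that a more severe event never has a weaker explicit category than a less severe one. One way is to drop the non-haematological restriction from both grade 4 items.

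The cost is a few words in the protocol and the reporting form, made through the route under Protocol amendments, and possibly a few more grade 4 reports. No change to the design or the analysis is needed.

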#### Interim analysis

Safety interim analysis and futility interim analysis will be conducted every 8 months, and analysis report will be submitted to the Efficacy and Safety Evaluation Committee. The specific contents of the report include the following: ineligible patients/potentially ineligible patients, reasons for end of treatment/discontinuation/study protocol, adverse events and serious adverse events, completion rate of laparoscopic surgery, proportion of conversion to laparotomy, enrolled protocol deviations, disease-free rate/disease-overall survival rate of all participants, etc. The Efficacy and Safety Evaluation Committee will review and discuss the report in accordance with the procedures documented in the Clinical Safety Information Management Guidelines and make written recommendations to the study director including whether to continue the enrollment of the study.

#### Protocol amendments

The protocol can be amended after discussion and adoption by the study committee meeting, provided that the amendment of the protocol will not cause medical or financial burden or additional risk to enrolled patients. Any changes to the protocol must be identified in writing and signed by the trial director. Significant changes require approval of Institutional Review Board. The updated protocol will be uploaded to the clinical trial registry and copied to clinical investigators.

